### Sample size

Determination of the sample size for this study is based on data from a RCT examining the effects of a structured 6-week Goal Management Training
[17]. In each group 32 participants are required to detect an effect size of *d =* .6 with a power = .80 and α. = 05. These estimated sample sizes are comparable with other studies evaluating the efficacy of different types of GMT
[17,54].

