### Randomization and blinding

Allocation of participants to either condition will be established using a computer generated block randomization procedure (block size n = 4) without stratification. The written information to inform patients about the study only mentions that two types of GMT will be compared. To achieve participant blinding, no information will be given about specific differences between the two conditions. Assessor blinding will be achieved by filming the (i)ADL task performance of the participants. All hints of treatment condition will be avoided and performance will be scored by research assistants who are not involved in delivering GMT.

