### Statistical analysis

All data will be analyzed with IBM SPSS 19. The normality of all variables will be checked and corrected for, if necessary. The performance on the neuropsychological tests will be compared with normative data and corrected for age and education. Descriptive statistics of relevant variables will be obtained and compared for the two treatment arms using analysis of variance.

To evaluate the efficacy of GMT-errorless learning compared to conventional GMT with trial and error learning, pre- and post training data will be analyzed using a 2 × 2 repeated measure analysis of variance (General Linear Model) with treatment condition (GMT-errorless learning and conventional GMT) as between-subject factor and measurement (pre- and post-treatment) as within-subject factor. The dependent variable will be the standardized scale score (quantitative). The same analysis will be done for the secondary outcome measure, the GAS scores. Appropriate post-hoc tests will be performed and effect sizes (partial eta-squared) will be computed. Moreover, correlations will be computed between moderator variables (questionnaires and neuropsychological tests) and treatment effects (difference score: post treatment minus baseline).

The background variables of the participants in both treatment conditions are expected to be comparable (age, education level, estimation IQ) because of the randomization procedure. In case of significant differences, appropriate statistical adjustment for confounding variables will be performed (ANCOVA). All statistical tests will be two-tailed, alpha set at 0.05.

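### Background covariates are adjusted for only if they differ significantly between the randomised arms, a rule that recovers almost none of the benefit of adjustment and should be replaced by covariates named in advance

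*Protocol article*

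**What the plan says.** All of this stands in the Statistical analysis section of the protocol article unless another section is named.

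- Primary model: "pre- and post training data will be analyzed using a 2 × 2 repeated measure analysis of variance (General Linear Model", with treatment condition and measurement as its only factors. The pre-treatment score enters as a repeated measure, not as a covariate.
- Baseline comparison: "Descriptive statistics of relevant variables will be obtained and compared for the two treatment arms using analysis of variance".
- Expectation: "The background variables of the participants in both treatment conditions are expected to be comparable (age, education level, estimation IQ) because of the randomization procedure".
- Trigger: "In case of significant differences, appropriate statistical adjustment for confounding variables will be performed (ANCOVA".
- Level: "All statistical tests will be two-tailed, alpha set at 0.05".

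The Randomization and blinding section describes a "computer generated block randomization procedure (block size n = 4) without stratification". No section fixes a covariate for the primary test in advance. The article therefore states a data-driven rule for choosing the model; this is not a detail merely left to a fuller plan.

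**The concern.** The rule rests on a test that cannot inform the decision. Arms are formed by computer-generated randomisation, so the null hypothesis of the baseline test is known to be true and a small p-value marks a chance event. Adjustment is worth making when a variable predicts the outcome, and the baseline p-value says nothing about that. The rule can bring in a variable of no prognostic value because it happened to differ. It can also leave out a strongly prognostic one because the difference fell short of 0.05.

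At stake is the precision of the primary comparison in a small trial, and a model that is settled only after baseline data have been compared by arm.

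**Working it through.** **Inputs.** From the article: 32 per arm, d = 0.6, power 0.80 (Sample size); two-sided 0.05 and three named background variables (Statistical analysis). Assumed, because the article does not give them: the correlation r of a covariate with change, and the pre–post correlation ρ.

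**1. The plan's own figure.** The article says "In each group 32 participants are required to detect an effect size of" 0.6 SD with 80% power. For two independent means, n = 2(1.96 + 0.8416)² / 0.6² = 2 × 7.849 / 0.36 = 43.6, so 44 per arm (45 with the t distribution). At 32 per arm the standard error is √(2/32) = 0.25 SD, and power is Φ(0.6/0.25 − 1.96) = Φ(0.44) = 67% (66% with t). So 32 is not reproduced if 0.6 is in SD units of the variable tested. If 0.6 refers to the SD of the post-treatment score, 32 would need ρ of about 0.63 for the planned change comparison (43.6 × 2 × 0.367 = 32.0), or about 0.52 for ANCOVA on baseline (43.6 × (1 − 0.27) = 31.8). The article states neither. This is a separate matter; here it shows only that there is little power to spare.

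**2. When the trigger fires.** The two-sided critical t on 62 degrees of freedom is about 2.0, so an observed difference must reach 2.0 × 0.25 = 0.50 SD. The chance that at least one of three independent tests fires is 1 − 0.95³ = 14.3%; 85.7% of trials stay unadjusted. For a single covariate the figure is 95%. Education and estimated IQ are likely to be correlated, which would put the share between these two.

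**3. What an untriggered imbalance can do.** A difference of 0.49 SD in a covariate with assumed r = 0.5 shifts the estimate by 0.49 × 0.5 = 0.245 SD, or 0.245/0.6 = 41% of the target effect, and is not adjusted for.

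**4. Power with one covariate.** In the 2 × 2 model the group-by-time test is a t-test on change scores, so r must be the correlation with change. Simulation with 32 per arm and d = 0.6 (8,000 trials per row, 10,000 for the last; simulation error about √(0.66 × 0.34/8000) = 0.5 point):

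| r (assumed) | Under the rule | Always adjusted | Gain |
|---|---|---|---|
| 0.1 | 66% | 65% | none |
| 0.2 | 66% | 67% | 1 point |
| 0.3 | 66% | 69% | 3 points |
| 0.5 | 66% | 77% | 11 points |
| 0.7 | 68% | 91% | 23 points |

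A run of 20,000 trials shows how little of the benefit the rule keeps. At r = 0.5, power is 65.7% never adjusted, 66.5% under the rule and 77.3% always adjusted: (66.5 − 65.7)/(77.3 − 65.7) = 0.8/11.6 = 7%. At r = 0.7 it is 65.5%, 67.3% and 90.9%: 1.8/25.4 = 7%.

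Three covariates that jointly explain 10%, 25%, 40% or 50% of the variance of change (40,000 trials each) give the same picture: 65.4% vs 68.0%, 66.3% vs 76.2%, 66.8% vs 84.6% and 67.0% vs 90.0%.

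**5. A trait equally related to both scores.** If pre = aC + e₀ and post = aC + e₁ + effect, then C cancels in post − pre. With r = 0.5 to both scores and ρ = 0.6, power was 67% unadjusted and 66% adjusted; a second run with a larger standardised effect gave 76% and 75%. Adjustment of the change score then gains nothing.

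**6. Type I error.** With one covariate under the rule: about 5% (4.8% to 5.1%) at r of 0.3 or less, 4.1% at 0.5, 3.9% at 0.7. The direction can be traced with three covariates explaining 25%. In the 14.2% of trials where the trigger fires, the unadjusted test would reject 9.3% of true nulls and the adjusted test 5.1%. The overall rate falls from 4.94% by 0.142 × (9.3 − 5.1) = 0.60 point, to 4.34%. The rule removes false positives in the triggered trials and changes nothing in the rest.

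**7. The baseline task score.** With unit variance at each time, the variance is 2(1 − ρ) for change and 1 − ρ² for ANCOVA, a ratio of (1 + ρ)/2, which is always below 1 for ρ < 1. Simulated power, change score vs ANCOVA: 51% vs 69% (ρ = 0.3), 65% vs 77% (0.5), 76% vs 84% (0.6), 86% vs 91% (0.7).

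**The case against.** The case for leaving the rule alone has real content.

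- Measured against the planned unadjusted model, the rule costs no power; it is level with it or slightly above. The loss appears only against a model that always adjusts. This stands: the rule fails to gain, it does not take away.
- Age, education and IQ are stable traits. They may predict how well a patient performs at both times without predicting improvement, and then adjustment of the change score gains nothing. This also stands, and the 11- and 23-point figures cannot serve as the expected loss.
- The main model is fixed and three variables are named, so there are few alternatives. This stands largely. A reader might infer that the final model is wholly open, but the article does not support that: most trials would end with the unadjusted analysis. Some discretion remains because the variables to be compared are described only as relevant ones.
- Most of the dependable gain comes from the baseline task score, which concerns the choice of primary model and not the trigger. This is correct, and that gain should not be charged to the trigger.

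A reader might also infer that choosing covariates by significance raises the false-positive rate. For the listed variables it does the opposite, slightly. Inflation would require covariates to be chosen after results were seen, and the article does not say that they will be.

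None of this defends the trigger. No value of r makes a between-arm p-value informative about prognosis.

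**Conclusion.** The point holds as a flaw of principle with a modest and uncertain cost. The significance trigger is uninformative under randomisation, misses differences below about 0.5 SD, and leaves about 86% of trials unadjusted if three independent variables are tested. It recovered about 7% of the available gain in power where there was a material gain to recover.

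The power forgone ranges from nothing to about 23 points over assumed correlations with change of 0.1 to 0.7. The article supports no particular value in that range, and a trait related equally to both scores gives no gain. The type I error is at or slightly below 5%, so the validity of a positive result is not threatened. The conclusion that the rule should go does not depend on r; only the size of the benefit does.

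**What to change.** Delete the significance trigger. State instead that, whatever the observed balance, the post-treatment task score will be analysed by ANCOVA with treatment condition, the baseline task score, and one or two covariates named now because they are expected to predict outcome (for example age or estimated IQ, both already collected). State also that baseline p-values will not be used to choose covariates. The Current study status section says that recruitment has begun, so the change should be recorded before any outcome is compared by arm.

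The cost is two sentences and one to three degrees of freedom. If the added covariates turn out not to be prognostic, the loss of power is negligible (66% vs 65% at r = 0.1 in the table above).

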## Discussion

Both Goal Management Training and errorless learning are two methods that have been separately well studied and shown to be effective. Up to now however, the two methods have never been combined. Combining an errorless learning approach with GMT is expected to optimize the acquisition of the GMT algorithm and improve the performance of complex daily tasks in brain-injured patients with executive deficits. Consequently, the efficacy of the intervention is increased, which may contribute to functional independence of patients with acquired brain injury. Not only does the combination of methods provide an evidence-based intervention for clinical practice, the present study may also contribute to more insight into the underlying mechanisms of errorless learning. Previous studies investigating errorless learning have often focussed on patients with profound memory impairments, such as patients with Alzheimer’s disease or Korsakoff’s syndrome
[26,30]. The assumption was that due to a dysfunctional explicit memory system errors were not consciously corrected and implicitly consolidated
[31]. However, the beneficial effects of errorless learning may also be related to a failing error monitoring system. That is, the inability of patients with executive dysfunction to detect errors
[38]. The current study proposal focuses on patients with primarily executive impairments in whom the presence of memory impairments is less prominent. This suggests that explicit memory is relatively spared in these patients, whereas their error-monitoring system is failing. As a result, the current study may contribute to a better understanding of these two underlying mechanisms of errorless learning.

Previous studies evaluated GMT used paper-and-pencil tasks
[7] or fixed (i)ADL tasks, such as meal preparation
[7] and financial management
[15]. A strength of this study is that participants will choose their own individual (i)ADL tasks that will be (re)learned during the training. Individual goals correspond to individual lifestyles and demands and may therefore provide a more fitting contribution to daily functioning and enhance functional independence of the participants.

In summary, the aim of the study is to examine the efficacy of Goal Management Training combined with an errorless learning approach as a treatment of executive problems in patients with acquired brain injury in the chronic phase, focusing on execution of complex daily-life tasks. This study could contribute to a better treatment of executive deficits in cognitive rehabilitation.

### Current study status

The errorless learning in Goal Management Training trial has started recruitment from June 2012.

## Abbreviations

ABI: Acquired brain injury; BADS: Behavioural assessment of the dysexecutive syndrome; CFQ: Cognitive failures questionnaire; CFT: Category fluency test; DEX: Dysexecutive questionnaire; EFI-NL: Executive function index (Dutch version); EOS: Executive observation scale; GAS: Goal attainment scaling; GMT: Goal management training; (i)ADL: (Instrumental) Activities of daily living; IQ: Intelligence quotient; LFT: Letter fluency test; LNS: Letter-number sequencing; NART: National adult reading test; RAND-36: RAND-36 item short form health survey; RBMT III: Rivermead behavioural memory test-third edition; SD: Standard deviation; SPSS: Statistical package for the social sciences; SMART: Specific measurable attainable reasonable timely; TAP: Test for attentional performance; WAIS III: Wechsler adult intelligence scale-third edition
